### Specific Objectives:

- To describe the sociodemographic and clinical characteristics of patients with invasive mechanical ventilation in the Neurological Intensive Care Unit at Fundación Santa Fe de Bogotá.
- To evaluate the efficacy of early multimodal therapy versus late multimodal therapy in terms of ventilator-free days and other secondary outcomes.

- To establish the sociodemographic and clinical factors associated with the type of therapy (early or late) the primary outcome (ventilator-free days) and secondary outcomes.
- To evaluate the safety of early multimodal therapy versus late multimodal therapy in terms of adverse events, serious adverse events, episodes of broncho-aspiration, and healthcare-associated pneumonia.
- To evaluate the impact of different predefined subgroups, such as the type of respiratory failure (hypoxemic or hypercapnic) and the type of patient (surgical, respiratory, burn, cardiovascular), on the primary outcome results.

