## 6.6. Outcomes

### *Effectiveness*

Main outcome: time (days) from intubation to extubating.

- Secondary outcomes:

- Days free of mechanical ventilation until day 28
- Days of delirium until day 28
- Time in ICU with delirium until day 28
- Days of hospitalization with delirium until day 28
- Days of sedation until day 28
- Sedation-free days until day 28
- Extubating failure
- Need for non-invasive mechanical ventilation
- Exploratory outcomes:
- Barthel index at discharge
- Days of hospital stay
- Length of stay in ICU
- Mortality from any cause up to 90 days
- Time from intubation to start of therapy
- Muscular strength measured with the Medical Research Council (MRC) scale
- Dysphagia 72 hours after extubation
- Dysphonia 72 hours after extubation
- Time until initiation of oral administration post-extubation
- Development of healthcare-associated pneumonia,
- Maximum mobility measured by JH-HLM
- Grip strength
- Cognitive function measured using the Montreal Cognitive Assessment (MOCA)
- Evaluation of functionality in daily activities until day 28
- Quick sensitivity and dexterity test

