### 6.13. Statistical Analysis Plan

A Shapiro-Wilk test will be conducted to verify the distribution of quantitative variables, considering the number of patients included. Data will be presented as means or medians, accompanied by their standard deviation or interquartile range, as appropriate. Categorical variables will be described as absolute and relative frequencies.

To compare continuous variables between the two groups (early vs. late therapy), a T-test or the Mann-Whitney U test will be employed, depending on the distribution of the data. For categorical variables, a  $\chi^2$  test or Fisher's exact test will be used, as appropriate.

The primary objective of the study is to evaluate the association between the use of early multimodal therapy and the days of invasive mechanical ventilation. To address this question, we will perform a survival analysis and a Cox regression. A risk variable will be created by combining the time of invasive mechanical ventilation and extubation (yes/no). Then, a univariable Cox regression analysis will be performed with the risk variable as the dependent variable and the intervention group (early vs. late) as the independent variable. Additionally, a survival curve will be generated, and differences between the two groups will be analyzed using a log-rank test.

To evaluate factors related to the time of mechanical ventilation, univariable Cox regression models will be performed for all variables included in the study. To determine whether continuous variables can be evaluated continuously or as categorical variables, the assumption of linearity will be checked through the Martingale residual plot. If linearity is not met, the variable will be stratified, and cut-off points will be defined according to the appearance of the plot. Subsequently, those variables with a statistically significant p-value (less than 0.25) and clinically important variables (age, sex, delirium, etc.) will be included in a multivariable Cox regression model. The best model will be selected through a Backward Stepwise process based on Akaike (AIC) and Bayesian (BIC) information criteria.

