Variables that could act as confounding factors will be evaluated through a second multiple regression model. In this model, the potentially confounding variable will be removed, and the resulting slope or estimator (adjusted estimate) will be calculated. If there is a change greater than 15%-20%, the confounding variable will be included in the final model. Otherwise, the most parsimonious model will be chosen.

To evaluate the interaction between two variables, another regression model will be performed, including a new variable resulting from multiplying the two potentially interacting variables. If the regression coefficient of this new variable has a significance level of less than 0.05, it is concluded that there is an interaction, and this variable will be included in the model. Variables with potential interaction will be identified by evaluating confounding factors. Researchers will also evaluate clinical variables that may be considered as interaction or confounding variables through the above-described strategy.

The assumption of proportional hazard will be evaluated using Schoenfeld residuals, and influential values will be analyzed through residuals versus observations plots. Multicollinearity will be assessed through matrix curves.

Logistic regression models will be used to assess the relationship between our dichotomous variables, such as failed extubation, post-extubation NIV, prolonged mechanical ventilation, tracheostomy, and dysphonia, and the other studied variables. The assumptions of a logistic regression model, such as linearity in the log of the odds, independence of errors, homogeneity of variance, absence of multicollinearity, absence of outliers, and proportionality of effects, will be evaluated through residual analysis and graphical diagnostics, such as Pearson residual analysis or deviance residual analysis.

A multiplicity adjustment strategy will be employed in statistical tests, such as the Bonferroni method, Holm-Bonferroni, or other methods that control the false discovery rate (FDR), to maintain the overall type 1 error rate at an acceptable level.

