A detailed exploration will be conducted through a sensitivity analysis of possible interactions between identified subgroups, according to the RASS scale, protocol adherence, and other relevant variables, to deepen the understanding of any joint influence that may affect the study results. If no statistically significant differences are identified through regression analyses, a post-hoc analysis will be conducted to assess whether the recruited sample size was adequate to detect possible differences between the established subgroups. This additional analysis will allow adjusting the interpretation of the results and provide valuable information on the validity of the obtained conclusions.

Finally, an independent data monitoring committee will be established to conduct interim reviews of the sample size, allowing adjustments based on variations in event rates observed during the study, thus ensuring adequate statistical power throughout its execution.

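### The multivariable Cox model admits post-randomisation variables, including delirium, and picks covariates from the data, so a treatment effect quoted from it is unreliable; the primary univariable comparison is unaffected

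*Protocol*

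**What the plan says.** All references are to the Protocol. Section 6.13 is its own statistical analysis plan, and the Summary repeats it.

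- **Primary comparison.** To address the primary objective, "a univariable Cox regression analysis will be performed with the risk variable as the dependent variable and the intervention group (early vs. late", as the only covariate. A log-rank test accompanies it.
- **Second model.** The next paragraph has a different purpose: "To evaluate factors related to the time of mechanical ventilation". For this, "univariable Cox regression models will be performed for all variables included in the study". Continuous variables that fail linearity are cut at points read from the residual plot. Variables with p below 0.25 "and clinically important variables (age, sex, delirium, etc.) will be included in a multivariable Cox regression model". Backward stepwise selection by AIC and BIC follows.
- **Confounder step.** "If there is a change greater than 15%-20%, the confounding variable will be included in the final model". The text does not say which coefficient is monitored. Interactions with p below 0.05 are also added.
- **Delirium.** Section 6.6 lists "Days of delirium until day 28" as a secondary outcome. Section 6.7 records delirium daily during ICU observation.
- **Exploration.** A sensitivity analysis looks at interactions between subgroups "according to the RASS scale, protocol adherence, and other relevant variables".
- **Objective.** One specific objective in section 5 reads "To establish the sociodemographic and clinical factors associated with the type of therapy (early or late"), and links those factors to the primary and secondary outcomes as well.

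**The concern.** In a randomised comparison, a covariate measured after allocation may itself be changed by the treatment. Adjusting for it removes the part of the effect that passes through it. If the covariate and the outcome share an unmeasured cause, such as severity, adjustment can also create a difference where there is none. Here the candidate list is open to such variables, and delirium is named for entry whatever its p-value.

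Separately, choosing covariates by their association with the same outcome and then reporting an ordinary p-value ignores the selection. With 74 patients and a long candidate list, the reported standard error is too small.

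At stake is the adjusted treatment effect that a report would naturally print beside the primary result. It could dilute a real benefit or suggest a false one. No sentence says that it carries no confirmatory weight.

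**Working it through.** **Step 1. What the candidate list contains.** The variable table in section 6.11 lists about 80 variables besides study group. Taken literally, the candidates include:

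- *Variables arising after allocation:* delirium and delirium days, sedation days, tracheostomy, healthcare-associated pneumonia, weaning measures. Several accumulate with time on the ventilator, so they may also be consequences of the outcome.
- *The outcome restated:* days of mechanical ventilation, and ventilator-free days, defined as 28 minus ventilation days.
- *The randomised factor:* time from intubation to start of therapy. The comparator entry in section 3 says the arms differ only in this interval.
- *Proper baseline variables:* age, sex, admission severity scores, ventilator settings at intubation.

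No sentence limits the model to the last group, and none says that study group is retained through selection.

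**Step 2. Error rate after selection.** The plan gives no figure for this model. From the documents: 74 patients, 37 per arm; alpha 0.05; screen at p < 0.25. Assumed: no treatment effect, 20 or 40 independent noise candidates, about 15% censoring, group kept in the model, backward AIC. There were 400 simulated trials per setting.

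| Candidates | Expected to pass screen | Mean passing | Mean kept | Type I error, univariable | Type I error, selected model |
|---|---|---|---|---|---|
| 20 | 20 × 0.25 = 5 | 5.1 | 3.1 | 0.050 | 0.093 |
| 40 | 40 × 0.25 = 10 | 10.2 | 5.7 | 0.048 | 0.128 |

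The simulation standard error is √[p(1−p)/400]: about 0.014 for the first selected-model value and 0.017 for the second. The univariable test reproduces the planned 5%; the selected model does not. A separate run of 1,801 null trials with 25 candidates, 3 of them prognostic, gave 10.0% against 4.8%. The plot-chosen cut-points, the BIC, the change-in-estimate rule and the interaction tests were not simulated.

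**Step 3. Adjusting for delirium when it lies on the pathway.** A hazard ratio above 1 means faster extubation. Assumed: delirium in 60% of the late arm and 30% of the early arm; nominal total log hazard ratio L = ln 2 = 0.693. Delirium coefficient = −share × L / (0.60 − 0.30). Direct log effect = (1 − share) × L. There were 1,500 trials per setting.

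- *Half through delirium:* coefficient −0.5 × 0.693/0.30 = −1.155 (delirium HR 0.32); direct HR = exp(0.347) = 1.41. Mean treatment HR is 1.83 unadjusted and 1.43 adjusted. The rejection rate falls from 60% to 24%.
- *All through delirium:* coefficient −0.693/0.30 = −2.31 (delirium HR 0.10); direct HR 1.00. Mean treatment HR is 1.67 unadjusted and 0.99 adjusted. The rejection rate falls from 41% to 6%.
- *Milder version, all through delirium:* 60% against 35%, delirium HR 0.5. The expected log HR is about 0.25 × 0.693 = 0.173, or HR 1.19. Simulated values (3,000 trials) are 1.17 unadjusted and 1.00 adjusted.

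In each case the adjusted model recovers only the direct effect.

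**Step 4. Bias in the other direction.** Assumed: therapy lowers delirium but has no effect on ventilation time, and unmeasured severity raises delirium and slows extubation. Mean HR is 1.00 unadjusted and 0.86 adjusted. Type I error is 0.059 unadjusted and 0.099 adjusted (1,500 trials). Adjustment has created an apparent harm.

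**The case against.** The strongest reply is that the protocol does not use this model to judge the treatment. Section 6.13 assigns the primary question to the univariable Cox model and log-rank test, and introduces the stepwise model for factors related to ventilation time. That stands. A reader might infer that the trial's treatment conclusion loses its error rate, or that nothing says which analysis answers the primary question. The documents support neither reading.

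Three further readings also go too far:

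- *Delirium is locked into the model.* It enters whatever its p-value, but backward selection may remove it.
- *There is no confounding to look for.* That is true of the randomised contrast. In a prognostic model, factors can confound one another.
- *The objective on factors associated with type of therapy can test only chance.* That holds for baseline factors. Clinical factors arising later may differ because of treatment.

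The reply does not close the point. A confounder rule needs a target coefficient, and with none named, study group is an obvious candidate. The Summary puts the whole sequence under its primary plan of analysis. Section 6.13 makes a later step depend on significance in the regression analyses generally. Section 6.10 defines failure by lack of a significant difference without naming the deciding model. The multiplicity sentence chooses no method and is not tied to the selected model. An exploratory label could sit in a separate SAP, but the open candidate list and the naming of delirium are rules this document states.

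**Conclusion.** The concern holds for any treatment effect read from the multivariable model, and only for that. Followed as written, the rule lets that effect be conditioned on consequences of therapy, on the outcome restated and on the randomised factor, and then selects covariates from the same data.

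Under the stated assumptions, type I error from selection alone is about 9% to 13% instead of 5%. Adjustment for delirium takes the hazard ratio from 1.83 to 1.43, or from 1.67 to 0.99, according to how much of the effect passes through it. The delirium rates, strength of association, censoring, number of candidates and retention of study group are assumptions, not protocol figures, so the sizes are illustrative. In particular, the full-mediation case with delirium HR 0.10 is extreme. The mechanism does not depend on those values, and the direction of bias can go either way. This should be corrected before analysis, but it does not invalidate the primary test.

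**What to change.** Change the wording of section 6.13 and the matching Summary text:

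1. State that the univariable Cox model, or a fixed Cox model adjusted for the sex and age randomisation strata, is the sole confirmatory treatment analysis.
2. Limit any adjusted treatment estimate to prespecified baseline covariates, with no data-driven selection.
3. Remove delirium and every other post-randomisation variable from the candidate list, including ventilator-free days and time from intubation to therapy. Delirium remains a secondary outcome.
4. Label the stepwise model exploratory and prognostic, and state that no treatment conclusion is drawn from it.
5. In the exploratory subgroup analysis, use RASS at randomisation. Do not use adherence as a treatment-effect subgroup: section 6.9 defines it by later events such as withdrawal, transfer or receiving too few sessions. The planned per-protocol sensitivity analysis can remain as a separate item.

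Adding baseline severity to the primary model or deleting the objective on factors is not needed to cure this defect.

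The cost is a protocol or SAP text change, with no extra patients or data and somewhat less analysis.

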|                                                                          | hypercapnic) and the type of patients (surgical, respiratory, burned, cardiovascular), on the results of the main outcome.                                                                                                                                                                                                                                                                                                                                                                                                                                                                                                                                                                                                                                                                                                                                                                                                                                                                       |
| NUMBER OF SUBJECTS                                                | 37 for each group and 74 in total.                                                                                                                                                                                                                                                                                                                                                                                                                                                                                                                                                                                                                                                                                                                                                                                                                                                                                                                                                               |

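### Interaction candidates are chosen by a confounding screen, which is the wrong criterion for effect modification and does not fit the subgroup objective

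*Protocol*

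**What the plan says.** Section 6.13 sets out two procedures in succession. The first judges confounding by change in estimate: a variable is removed from a multivariable model and the estimate recalculated. The rule is "If there is a change greater than 15%-20%, the confounding variable will be included in the final model". The second judges interaction by a product term: "If the regression coefficient of this new variable has a significance level of less than 0.05, it is concluded that there is an interaction".

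The two are then joined: "Variables with potential interaction will be identified by evaluating confounding factors". The next sentence adds a second route: "Researchers will also evaluate clinical variables that may be considered as interaction or confounding variables through the above-described strategy". The Summary (Section 1) carries equivalent text.

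Two other places bear on the same question. The Specific Objectives in Section 5 include "To evaluate the impact of different predefined subgroups, such as the type of respiratory failure (hypoxemic or hypercapnic") and the type of patient, with the primary outcome as the target. A later paragraph of Section 6.13 plans a "sensitivity analysis of possible interactions between identified subgroups, according to the RASS scale, protocol adherence, and other relevant variables", with no screen mentioned. The sample is "37 for each group and 74 in total".

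**The concern.** Whether a variable confounds and whether it modifies the effect are different questions. The change-in-estimate screen asks whether leaving a variable out moves the overall treatment estimate. Effect modification asks whether the treatment effect differs between levels of that variable. A variable can do either without the other.

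Under 1:1 randomisation, baseline imbalance arises only by chance. What moves the estimate is then chance imbalance combined with prognostic strength, plus the non-collapsibility of the hazard ratio. A treatment estimate near zero also inflates any relative change. None of these indicates modification.

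At stake is the subgroup objective in Section 5. If the sentence is followed as written, a subgroup factor may never reach its interaction test because it did not shift the overall estimate, while a factor of no interest as a modifier may be tested because it did.

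**Working it through.** The plan gives no figure for interaction power, so there is nothing to reproduce. The screen was checked by simulation.

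**From the protocol:** 74 patients, 1:1 allocation, Cox model for time to extubation, cut-offs of 15% and 20%, product term tested at 0.05 (taken as two-sided).

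**Assumed:** a binary factor with 50% prevalence, exponential times, censoring of about 20% at the baseline hazard, and 1,000 trials per scenario. Change is measured on the log hazard ratio:

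change = |b without factor − b with factor| / |b with factor|

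The interaction test is the Wald test of the product term. In the table, the first column gives the treatment HR in the two factor levels, and the second the HR of the factor in the late arm.

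| Treatment HR by level | Factor HR, late arm | Passes 15% | Passes 20% | Direct test | 15% screen, then test | 20% screen, then test |
|---|---|---|---|---|---|---|
| 1 vs 2 | 1 | 47% | 39% | 25% | 16% | 13% |
| 1 vs 2 | 0.5 | 42% | 33% | 24% | 12% | 10% |
| 1 vs 3 | 1 | 67% | 55% | 54% | 44% | 37% |
| 1 vs 3 | 0.5 | 25% | 19% | 53% | 17% | 13% |
| 1 vs 4 | 1 | 76% | 66% | 72% | 59% | 53% |
| 1 vs 4 | 0.5 | 20% | 13% | 72% | 17% | 11% |
| 1 vs 1 (no modifier) | 1 | 36% | 30% | 5% | 2% | 2% |
| 1 vs 1 (no modifier) | 0.5 | 71% | 65% | 6% | 5% | 4% |

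The two rows for HR 1 vs 4 show the mechanism. With a factor HR of 0.5 in the late arm, the factor HR in the early arm is 0.5 × 4 = 2. The average over arms is √(0.5 × 2) = 1. The factor has no average prognostic effect, so dropping it barely moves the treatment estimate and the screen discards it. With a factor HR of 1 in the late arm it is 4 in the early arm, with average √(1 × 4) = 2. The same interaction then usually passes, because the factor is prognostic on average.

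Over all scenarios run, true modifiers passed the 15% screen in 6% to 77% of trials and non-modifiers in 6% to 71%. The lowest figure for a modifier was HR 1.5 vs 4 with factor HR 0.5; the highest was HR 0.67 vs 2 with factor HR 1. The two ranges almost coincide.

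The fault does not vanish with size. At 740 patients, HR 1 vs 4 with factor HR 0.5 passed the 15% screen in 0% of trials although its product term was significant in 100%.

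Repeats of the HR 1 vs 4 case agree. One set (3,000 trials, about 25% censoring) gave 69-71% for the direct test, 15-58% after the 15% screen and 11-51% after the 20% screen. Another gave 70-75%, 18-60% and 12-52%.

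**The case against.** Several points on the other side stand.

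- A reader might infer that true modifiers are mostly lost. The results do not support that. In the scenario where the factor has no effect in the late arm, about two thirds to three quarters of modifiers with HR 1 vs 4 pass. The loss depends on a main effect that nobody knows in advance.
- A reader might infer that the screen is the only way to an interaction test. The protocol does not say so. For clinically chosen variables, the strategy referred to could be the product-term test alone, and the later exploration in Section 6.13 mentions no screen. That paragraph also speaks of identified and established subgroups, which can be read as those in Section 5. What remains is an ambiguity between three places.
- A reader might infer that the screen produces false claims of interaction. It does not. Passing only earns a test at 0.05. With no treatment effect and no interaction, a factor both passed and was significant in about 2-5% of trials, and Section 6.13 also plans a multiplicity adjustment. The rates at which non-modifiers pass depend on the scale, which the protocol leaves open: on the hazard ratio itself they are about 0-32%, though that scale also drops more true modifiers.
- A reader might take RASS to be a post-treatment variable. Section 6.5 uses it to decide which maneuvers to give, so a first value may precede the first session. The protocol does not state which value enters the interaction analysis.
- The simulation compares models with and without one factor, whereas Section 6.13 removes a variable from a multivariable model.

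None of this makes change in estimate a measure of effect modification.

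**Conclusion.** The concern holds in this limited form: the confounding screen is the wrong criterion for choosing interaction candidates. It can drop strong modifiers and admit non-modifiers, and the sentence in Section 6.13 must be reconciled with the objective in Section 5 and with the later exploration in Section 6.13. For HR 1 vs 4, power falls from about 70-75% to about 11-53% (20% screen) or 15-60% (15% screen), under the assumptions stated above. The case is a favourable one, a binary factor split in half. The type of patient has six codes in Section 6.11, an average of 74/6, or about 12, patients per code.

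The adherence point holds separately. Section 6.9 defines low adherence by withdrawal, unrelated adverse events, transfer, or failure to receive 80% of the required interventions, all of which occur after randomisation. For RASS the fault is unstated timing, and no RASS value appears among the admission measurements in Section 6.7 or in the start-of-study list in Annex 4.

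The consequence is confined to secondary modelling. The primary univariable Cox and log-rank comparison is unaffected, and power for modest interactions is low with or without the screen.

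**What to change.** Replace the sentence in Section 6.13, and its counterpart in the Summary. For each subgroup factor named in Section 5 (type of respiratory failure, type of patient), test the treatment-by-factor term directly in the Cox model, with no confounding screen. Report the hazard ratio in each subgroup with its 95% confidence interval and label these analyses exploratory.

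Fix the timing of both factors: classify them from the patient's status at intubation, before randomisation. This matters because Section 6.11 words the type of respiratory failure as something that develops, and Annex 4 does not list it at the start of the study.

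In the later exploration, do not treat protocol adherence as an effect modifier. Use RASS only if a pre-randomisation value is available; otherwise drop it.

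The cost is mainly analysis wording. A pre-randomisation RASS would need a new data field, and dropping RASS avoids that. The downside is a few prespecified tests of low power, about 25% for HR 1 vs 2, in place of a data-driven search.
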